### Provisions for posttrial care {30}

There will be no provision for patients who participated in the trial. Posttrial care followed the usual standards of care after gastric cancer surgery.

### Outcomes {12}

The primary outcome of this trial was the QoL of the gastric cancer survivors (KOQUSS-40). The KOQUSS-40 questionnaire was developed and validated to evaluate the QoL of patients with gastric cancer who underwent gastrectomy. The questionnaire included 40 items across 11 domains, focusing on QoL related to postgastrectomy symptoms^[16]^. Using this questionnaire, we will compare each item and domain score between the groups before surgery and at 1, 3, and 6 months after surgery in the outpatient clinic.

Weight, nutritional parameters, questionnaire compliance, self-efficacy, and physical activity were compared between groups as secondary outcomes. Nutritional parameters, such as hemoglobin, albumin, and lymphocytes, and the prognostic nutritional index will be measured using common laboratory tests. Information on satisfaction with the Wecare^®^ program will also be collected.

### Participant timeline {13}

The participant timeline is shown in Figure 3.

**Figure 3. F3:**
[figure not shown]
Timeline of the study period.

### Sample size {14}

This pilot study primarily aimed to evaluate the feasibility and preliminary efficacy of the intervention; hence, formal sample size calculation based on statistical power was not performed^[17]^. However, the sample size of 88 participants was determined based on prior feasibility studies and expected effect sizes derived from previous QoL-related interventions. The initial cohort of 22 patients was used to optimize the protocol, followed by a randomized allocation of the remaining 66 participants.

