**Methods::**

A total of 88 patients who undergo gastrectomy for gastric cancer will be randomly allocated to either the “Wecare^®^” group or the control group at a 1:1 ratio. After using the “Wecare^®^” platform for the first 22 patients and making modifications, the next 66 patients will be randomized equally. The primary outcome of this trial is the QoL among gastric cancer survivors (KOQUSS-40). The values of weight change, nutritional index change, KOQUSS-40 questionnaire compliance, self-efficacy, physical activity change, and satisfaction will be compared between the two groups as secondary outcomes. The investigator will follow-up with the patients at 1, 3, and 6 months after surgery at the outpatient clinic.

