### Intervention description {11a}

To understand the feasibility of participant recruitment or study design at all participating sites, we planned to determine the number of participants in two phases. In the first phase, 22 patients will be recruited from 11 institutions (two patients per institution) to collect patient data using the draft protocol and correct any problems, and 66 patients will be recruited from 11 institutions (6 patients per institution) to measure outcome variables preoperatively and at 1, 3, and 6 months postoperatively, according to the revised protocol. The number of subjects required for the main study was calculated based on the data from the second phase. Each participating hospital is expected to enroll a sufficient number of eligible patients because the incidence of gastric cancer in South Korea is very high and participating institutions perform a large number of gastric cancer surgeries each year.

The Wecare® platform aims to improve postoperative quality of life through multiple integrated mechanisms. Patient-reported outcomes are collected via the KOQUSS-40 questionnaire at regular intervals, enabling continuous monitoring of physical, psychological, and social symptoms. Based on these responses, the platform delivers algorithm-based personalized content, including tailored educational resources (text, image, and video formats) and automated feedback aligned with each patient’s symptom profile and recovery phase. The platform stratifies symptoms by severity and provides immediate guidance or recommendations for self-management. These results are also shared with physicians before outpatient visits, facilitating more informed clinical decision-making. This integrated, patient-centered digital approach is expected to promote self-efficacy, reduce symptom burden, and ultimately enhance overall QoL following gastrectomy.

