## Statistical methods

### Statistical methods for primary and secondary outcomes {20a}

Intention-to-treat (ITT) analysis, which includes all patients who are randomly assigned, will be used for primary and secondary outcomes. ITT analyses provide a conservative estimate of the treatment effect and identify statistically significant differences. If consent withdrawal or dropout occurs during follow-up, the data up to the time of consent withdrawal or dropout will be used. Comparative analyses of dropout rates by arm will also be conducted. Adherence to the Wecare^®^ program will be assessed under two conditions: Wecare^®^ webpage visits and completion of the KOQUSS-40 questionnaire on the Wecare^®^ webpage. Participants who visited the webpage at least once a month during the study period and completed all questionnaires on the webpage at 1, 3, and 6 months after surgery were considered to have high adherence and were included in the per-protocol analysis. A per-protocol analysis will also be performed to evaluate the treatment effect with high compliance.

The demographic data and baseline characteristics of all randomized participants will be presented as means and standard deviations for continuous variables and as frequencies and percentages for categorical variables. A summary of the primary and secondary outcomes will also be provided, which will be compared at each time point using the chi-squared test, Fisher’s exact test, Student’s t-test (two samples), or Mann–Whitney U test, as appropriate. The primary outcome variable (QoL) will be assessed using a linear mixed model to account for the clustering of four measurements in a single patient to evaluate the effect of the Wecare^®^ intervention. For the secondary outcome variable, we present the results of between-group comparisons, considering the same clustering.

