### Interim analyses {21b}

We do not have any plans to conduct interim analyses because this trial does not cause harm to patients. However, the platform could be modified after analyzing the results of the first 22 patients.

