## Discussion

This randomized controlled trial aimed to analyze the efficacy of a symptom management platform (Wecare^®^) among gastric cancer survivors across nine institutions in the Republic of Korea. The primary objective of this study was to determine the QoL (KOQUSS-40) of gastric cancer survivors after gastrectomy. To the best of our knowledge, this is the first study to verify the efficacy of web-based platforms in relieving discomfort after gastric cancer surgery.

Patients who have undergone gastrectomy for gastric cancer experience changes in their daily lives. Several tools have been introduced to assess QoL in gastric cancer patients, such as the European Organization for Research and Treatment of Cancer Quality of Life Questionnaire (EORTC QLQ-STO22), Functional Assessment of Cancer Therapy-gastric (FACT-Ga), and Post Gastrectomy Syndrome Assessment Scale (PGSAS-45)^[18,19]^. Due to limitations in being unable to comprehensively encompass or statistically verify patients’ gastrointestinal symptoms, the KOQUSS developed and validated the KOQUSS-40 questionnaire^[16]^. The symptom management platform (Wecare^®^) not only provides information about stomach cancer but also checks the patient’s discomfort through the KOQUSS-40 questionnaire and automatically provides a solution according to the patient’s symptoms based on the answers to the questionnaire. Wecare® is expected to not only address patients experiencing discomfort after surgery but also help reduce medical costs by eliminating unnecessary outpatient visits.

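### The protocol gives two randomised totals, 88 and 66, so the intention-to-treat set for the primary comparison is not fixed

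*Protocol article*

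**What the plan says.** The Abstract's Methods paragraph opens with "A total of 88 patients who undergo gastrectomy for gastric cancer will be randomly allocated" to Wecare or control, 1:1. Its second sentence says that the platform is used for the first 22 patients and modified, and that the 66 who come next are then randomised equally.

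Sample size {14} agrees with the second sentence: "The initial cohort of 22 patients was used to optimize the protocol, followed by a randomized allocation of the remaining 66 participants". The same section gives the trial's size as 88.

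Intervention description {11a} describes two phases. In the first, 22 patients (two at each of 11 institutions) are recruited "to collect patient data using the draft protocol and correct any problems". In the second, 66 patients (six at each of 11) are followed under the revised protocol. That section places the outcome measurements, and the data for sizing the main study, in the second phase.

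Sequence generation {16a} randomises eligible patients 1:1 and does not mention phase. Statistical methods {20a} defines the analysis set: "Intention-to-treat (ITT) analysis, which includes all patients who are randomly assigned, will be used for primary and secondary outcomes". Interim analyses {21b} plans no interim analysis but adds that "the platform could be modified after analyzing the results of the first 22 patients".

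**The concern.** The ITT definition is sound in itself, but it takes its content from the number randomised, and the document prints two numbers. A reader of the Abstract's opening sentence would expect 88 patients in the primary comparison. A reader of Sample size {14} would expect 66. No section says how the first 22 are allocated or whether they enter the between-group analysis.

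The two answers lead to different trials. With 66, everyone in the comparison is treated under the revised protocol, but the comparison is a quarter smaller than the stated size. With 88, the sample is as large as stated, but a quarter of the Wecare arm received the platform as it stood before any modification, so the estimate no longer describes one version of the intervention. If the choice is left open until the data are in, it can be made with the results in view.

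**Working it through.** **1. The stated size.** From Intervention description {11a}: 11 × 2 = 22, 11 × 6 = 66, and 22 + 66 = 88. The sum is right. The fault lies in which of these patients are called randomised. The first group is 22/88 = 25% of the total.

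**2. The statements side by side.**

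| Place | What it implies |
|---|---|
| Abstract, Methods, first sentence | 88 randomised |
| Abstract, Methods, second sentence | 66 randomised, after the first 22 |
| Sample size {14} | 66 randomised, after the first 22 |
| Intervention description {11a} | 22 under the draft protocol; outcomes measured in the 66 under the revised one |
| Sequence generation {16a} | all eligible patients, no phase distinction |
| Statistical methods {20a} | ITT is everyone randomised, number not given |

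The Abstract's second sentence, Sample size {14} and Intervention description {11a} favour 66. The Abstract's first sentence states 88, and Sequence generation {16a} does not exclude it.

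**3. Precision if the ITT set is 66.** For a difference in means with n per arm and common standard deviation SD, SE = SD × √(2/n).

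- n = 44: √(2/44) = 0.213 SD
- n = 33: √(2/33) = 0.246 SD
- Ratio: √(44/33) = 1.155, so the standard error is about 15% larger.

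The document gives no effect size, SD or power for KOQUSS-40, so no power calculation can be reproduced. As an illustration only, take a two-sample t-test at one time point, two-sided 5%, 80% power and no dropout:

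- Normal approximation, (1.960 + 0.842) × √(2/n): 0.60 SD at 44 per arm, 0.69 SD at 33 per arm.
- With the t distribution: 0.604 SD at 44 per arm, 0.700 SD at 33 per arm.

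These are not the operating characteristics of the planned linear mixed model over four measurements.

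**4. What is estimated if the ITT set is 88.** With 1:1 allocation in both phases, the Wecare arm holds 11 + 33 = 44 patients, and 11/44 = 25% used the platform before modification. Let f be the effect of that version as a fraction of the later version's effect. The pooled effect is then (33 + 11f)/44 of the later version's effect: 75% at f = 0, 87.5% at f = 0.5 and 100% at f = 1. The document supports no value of f, so these figures show a range and are not an estimate of dilution.

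**The case against.** The strongest reply is that the text already has one coherent reading: a run-in of 22, then 66 randomised. On that reading the ITT definition needs no separate rule for the 22, because patients who were not randomised fall outside it, and the Abstract's 88 is loose wording. The trial is also called a pilot with no power-based size, and the flow diagram, which is not shown, may state how the 22 were allocated. Much of this stands, and it is why 66 is the favoured reading. It does not remove the problem, because two incompatible totals are printed and a pilot too must say who is randomised.

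Several stronger readings are tempting but not supported.

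- **Non-randomised patients will be pooled.** If the 22 all used Wecare without randomisation and were pooled, the comparison would be 55 v 33, with 22/55 = 40% of the Wecare arm non-randomised. Statistical methods {20a} rules this out. It could happen only if 88 were taken as the ITT total despite that definition.
- **Data that shaped the intervention are reused to test it, so the comparison is broken.** If the 22 were randomised, each phase remains a valid randomised comparison, and changing the platform later alters no data already collected. What remains is the averaging of two versions.
- **There is an undeclared interim efficacy analysis.** Interim analyses {21b} discloses the review of the first 22. No stopping rule, efficacy test or change of size is attached to it, and nothing says that between-arm KOQUSS-40 results drive the modification.
- **The size statement contradicts itself.** Sample size {14} denies a formal power calculation and then says "the sample size of 88 participants was determined based on prior feasibility studies and expected effect sizes". That is vague, but informal reference to effect sizes can coexist with having no formal calculation.

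**Conclusion.** The point holds as an inconsistency in the randomised total, and therefore in the ITT set, which is either 66 or 88. An unseen analysis plan or the condensed form of an article does not explain it, since nothing is merely left out: two different totals are stated. If 66 is right, the headline 88 overstates the randomised comparison (33 v 33), with a standard error about 15% larger than at 44 v 44. If 88 is right, about a quarter of the Wecare arm used the pre-modification platform and the estimate mixes two versions. The 15% follows from the counts alone, given a common SD and equal arms. The detectable differences also rest on the single-time-point t-test without dropout, and the 25% assumes 1:1 allocation within the first 22 and that the platform is in fact modified after them.

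A reader might infer that the randomised comparison is already compromised. The documents do not support that. They show an analysis set that has not been fixed.

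**What to change.** State once whether the first 22 are randomised, and bring the Abstract, Intervention description {11a}, Sample size {14}, Sequence generation {16a}, Statistical methods {20a} and Interim analyses {21b} into line with that statement.

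- **If they are not randomised** (the favoured reading): restate the randomised and ITT total as 66, 33 per arm. Report the 22 separately as a feasibility run-in, outside the between-group comparison.
- **If they are randomised:** keep them in the ITT set, include phase as a stratum or covariate in the mixed model, and give the analysis of the 66 under the revised platform alongside.

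In either case, say in Interim analyses {21b} that the review of the first 22 uses feasibility and usability data. If a detectable difference is quoted (about 0.70 SD at 33 per arm, 0.60 SD at 44), label it as an illustrative single-time-point t-test without dropout.

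A separate, minor correction: the Discussion describes the trial as running "across nine institutions in the Republic of Korea", whereas Study setting {9} and Intervention description {11a} give 11. At two and six patients per site, nine sites would yield 18 + 54 = 72, not 88.

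The cost is protocol wording and no extra patients. Under the first option the stated size of the comparison falls from 88 to 66. Under the second, the analysis gains one model term and one supporting analysis.

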### Recruitment {15}

Recruitment will be conducted through announcements in the outpatient departments of each participating institution. Investigators will contact patients who wish to participate in this clinical trial and determine participation based on the inclusion and exclusion criteria.

## Assignment of interventions: allocation

### Sequence generation {16a}

Eligible patients will be randomly assigned to either the control or experimental group in a 1:1 ratio. Medical statisticians will perform stratified randomization. This randomization will be performed based on an independent computer-based sequence generated from the implementation of the dynamic algorithm as the stratifying variable.

### Concealment mechanism {16b}

Randomization will be performed as block randomization with a 1:1 allocation. To achieve randomization, a computer-generated sequence methodology will be used, which will ensure that both the randomization methodology and the allocation sequence are concealed from both the investigator and participants.

### Implementation {16c}

Randomization will be performed by an independent medical statistician, who will generate a stratified randomization list for the allocation sequence. Investigators will enroll and assign participants to the interventions.

## Assignment of interventions: blinding

### Who will be blinded {17a}

Clinician and patient blinding is impossible because of the nature of the trial regarding whether or not to apply the Wecare^®^ platform. However, the outcome data will be analyzed by statisticians blinded to group allocation to reduce assessment bias.

### Procedure for unblinding if needed {17b}

Because the investigators and participants will be aware of the allocation group, unblinding will not be required.

## Data collection and management

### Plans for assessment and collection of outcomes {18a}

The baseline demographic, surgical, and pathological characteristics of the patients and outcome variables were collected. Demographic and clinical characteristics were collected using an electronic case report form based on the participants’ electronic medical records. In the intervention group, questionnaire-based data will be collected using tablets at every planned visit, where the electronic questionnaire will be designed to warn the respondent about any missing values or outliers. A written questionnaire was administered to the control group. Because the data will be stored in the data center of the KOCAS ecosystem, central edit checking will be performed for all input data. A manual review of patient data will be performed in case of any error from the edit check.

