## Methods: participants, interventions, and outcomes

### Study setting {9}

This study enrolled participants who underwent radical gastrectomy at 11 participating teaching hospitals in the Republic of Korea, one of the countries with the highest incidence of gastric cancer. This study was approved by the Institutional Review Board of the Hospital.

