### Eligibility criteria {10}

Patients with gastric cancer aged 19–75 years who are indicated for gastrectomy will be eligible for this study. To be included, the patient should be operable and gastric cancer should be surgically removable (stages I–III). Patients who could not be followed up regularly, were illiterate, or did not consent to participate in the study were excluded. In addition, patients with severe psychiatric disorders, significant comorbidities, inability to communicate effectively, or other medical or personal conditions deemed inappropriate for participation by their attending surgeon were also excluded. Informed consent was obtained from all participants.

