## Interventions

### Explanation for the choice of comparators {6b}

In the intervention group, the participants were asked to use the Wecare^®^ platform (Fig. 2A~I). The Wecare^®^ platform administers QoL questionnaires, including the KOQUSS-40, following gastrectomy for gastric cancer. Based on participants’ responses, the platform automatically generates expert recommendations from gastric cancer specialists based on participants’ responses according to the timing of surgery after gastrectomy (Fig. 2C~E). Furthermore, the Wecare^®^ platform offers educational materials for gastric cancer to address the participants’ questions about the disease (Fig. 2F~I). Participants will be free to use the platform but will be asked to visit the Wecare^®^ platform at least once a month and answer questionnaires. The participants will visit an outpatient clinic before surgery and at 1, 3, and 6 months after surgery.

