**Figure 2. F2:**
[figure not shown]
Screenshots from Wecare^®^ application used by patients. **A** shows the patient’s basic information. **B** displays the diet and NRS2002 results. **C** evaluates the scores for each domain of the KOQUSS-40 questionnaire, where white indicates no to mild symptoms, blue represents intermediate symptoms, and red shows severe symptoms. **D** compares the patient’s values in each domain with the average values of a small group matched for age, gender, and operation period within an existing patient group. **E** provides automated responses regarding education and treatment for domains showing severe symptoms. **F** contains recommended educational materials from medical professionals about symptoms based on the patient’s postoperative timeline. **G** features educational materials in a card news format, primarily composed of images. **H** provides educational materials centered on text. **I** consists of educational materials presented in video format.

In the control group, participants will be asked to complete written questionnaires in the outpatient clinic before surgery and 1, 3, and 6 months after surgery. Based on the questionnaires, the clinician provides a solution at an outpatient clinic. However, the Wecare^®^ platform is not available.

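### The pre-operative KOQUSS-40 is taken on tablet in one arm and on paper in the other, which implies that allocation precedes the baseline of an open-label, self-reported primary outcome

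*Protocol article*

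**What the plan says.** **Intervention arm.** Plans for assessment and collection of outcomes {18a}: "In the intervention group, questionnaire-based data will be collected using tablets at every planned visit". The tablet form warns the respondent about missing values and outliers. The planned visits are listed in Explanation for the choice of comparators {6b}: "The participants will visit an outpatient clinic before surgery and at 1, 3, and 6 months after surgery".

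**Control arm.** Section {18a}: "A written questionnaire was administered to the control group". The paragraph of {6b} after the Figure 2 legend gives the timing: "participants will be asked to complete written questionnaires in the outpatient clinic before surgery and 1, 3, and 6 months after surgery". No on-screen warnings are described for this form.

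**Blinding.** Sections {17a} and {17b} say that neither clinicians nor patients are blinded and that participants will be aware of their group.

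**Use of the baseline.** Outcomes {12} compares item and domain scores at the pre-operative visit and the three later ones. Section {20a} fits a linear mixed model to four measurements per patient, so the pre-operative score is one of them. Section {20b} plans subgroups that include baseline health status.

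**Order of events.** Sections {16a} to {16c} give the ratio, the method and who generates the list. They do not place randomisation relative to the baseline questionnaire or to surgery. Figures 1 and 3, where this would usually appear, are not shown in the text at hand.

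**The concern.** A baseline protects a comparison because it is measured before the treatment, or knowledge of it, can act. Here the text has the baseline form itself depend on the arm. Two things could then make the arms differ at baseline for reasons other than chance:

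- **Knowledge of the arm.** Several KOQUSS-40 items are open to mood and expectation: overall health (item 1), nervousness (30), depression (31), worry about recurrence (37). A patient told that a new support platform is coming, or is not coming, may answer them differently. Self-efficacy, a secondary outcome, is exposed in the same way.
- **Mode.** A tablet form that prompts for missing or outlying answers may yield different scores and different completeness from paper.

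Knowledge of the arm would remain a concern with a single device if allocation were still disclosed first, although the device difference is the text's only evidence that it is. At stake are contrasts that use the baseline as a reference, possibly the baseline health status subgroups, and the second-phase data, which section {11a} intends for sizing the main study.

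**Working it through.** **Step 1. The order implied by the text.**

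| Element | Wecare arm | Control arm |
|---|---|---|
| Pre-operative visit planned? | Yes, {6b} | Yes, {6b} |
| Form at that visit | Tablet with warnings, {18a} | Paper, {6b} and {18a} |
| Patient blinded? | No, {17a}, {17b} | No, {17a}, {17b} |

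Two different forms at one pre-operative visit require the arm to be fixed before that visit's questionnaire. That the patient also knows it by then is probable, not stated.

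**Step 2. Numbers per arm.** The plan's total reproduces: 11 × 2 + 11 × 6 = 22 + 66 = 88. The Abstract says 88 are allocated 1:1, then that the later 66 are randomised; Sample size {14} speaks of randomising the remaining 66. I therefore use 44 and 33 per arm. The plan gives no SD, effect size or correlation, so everything below rests on assumptions.

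**Step 3. How a baseline shift enters.** Let b be the between-arm shift in the baseline rating and c the shift in the follow-up rating caused by knowing the arm or by mode, both in SD units. Let r be the correlation between baseline and follow-up.

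- Change from baseline: bias = c − b
- Baseline-adjusted: bias = c − r·b
- Follow-up score alone: bias = c, with no contribution from b

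With b = 0.2 and r = 0.5:

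| Case | Change | Adjusted | Follow-up alone |
|---|---|---|---|
| Baseline only (c = 0) | −0.20 | −0.10 | 0 |
| Shift persists (c = 0.2) | 0 | +0.10 | +0.20 |

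So the sign and size depend on whether the shift persists. If it persists fully, a change contrast removes it.

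**Step 4. Type I error when only the baseline is shifted (c = 0).** Two-sided 0.05, normal approximation, SD 1 at each visit, r = 0.5. Standard error for change = √(2(1 − r))·√(2/n); for adjusted = √(1 − r²)·√(2/n).

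Example, n = 44, b = 0.2, change: SE = 1 × √(2/44) = 0.213; b/SE = 0.94; error = Φ(0.94 − 1.96) + Φ(−0.94 − 1.96) = 0.155.

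| b | Change, n = 44 | Adjusted, n = 44 | Change, n = 33 | Adjusted, n = 33 |
|---|---|---|---|---|
| 0.1 | 0.076 | 0.058 | 0.069 | 0.056 |
| 0.2 | 0.155 | 0.084 | 0.128 | 0.076 |
| 0.3 | 0.291 | 0.128 | 0.230 | 0.108 |

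For r from 0.3 to 0.7 at b = 0.2 and n = 44, the ranges are 0.125 to 0.228 (change) and 0.060 to 0.151 (adjusted). A baseline taken on one form before disclosure makes b = 0 by design, and the error stays at 0.05.

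**The case against.** **The order is inferred.** This stands as a limit. No section states when randomisation happens, and the timeline figure or the full protocol may settle it. The article also mixes past and future tense, so every planned visit might have been meant loosely. Even so, the control text names the pre-operative visit explicitly and the intervention text lists it among the visits, so arm-specific baseline collection is the natural reading.

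**The bias formulas are a special case.** This also stands. Bias of b or r·b requires that follow-up ratings are not shifted in the same way, and the trial is unblinded throughout. Section {20a} names neither a change score nor a baseline-adjusted model, only a mixed model on four measurements and tests at each visit. The tests at 1, 3 and 6 months are untouched by a baseline shift.

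**It is a pilot.** Section {14} sets feasibility and preliminary efficacy as the aim, without a power calculation. That lowers the stakes, but the remedy costs very little.

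**A stronger inference a reader might draw.** Eligibility criteria {10} takes patients "aged 19–75 years who are indicated for gastrectomy will be eligible", Study setting {9} says "This study enrolled participants who underwent radical gastrectomy", and section {20a} specifies "Intention-to-treat (ITT) analysis, which includes all patients who are randomly assigned". One might conclude that patients who never have a gastrectomy contaminate the analysis and that allocation should wait until after surgery. The documents do not support this as a defect. Keeping every randomised patient is what intention to treat means. Eligibility already requires operable, removable disease. If 1% to 5% of 88 had no gastrectomy (assumption), that is 0.9 to 4.4 patients; an assumed effect of 0.5 SD diluted by 5% lowers power at 44 per arm only from 0.65 to 0.61. Moving allocation after surgery is a debatable choice that would remove pre-operative platform access, and section {6b} describes general material on the disease as well as post-operative advice.

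**Conclusion.** The point holds in a limited form. Sections {6b} and {18a} together make the baseline of the primary outcome arm-specific, which implies that it is taken after allocation and, in this unblinded trial, probably with the arm known. Baseline-referenced contrasts in the mixed model, and possibly the baseline health status subgroups, are open to bias from knowledge of the arm or from mode.

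The direction and size cannot be determined from the documents. On assumed shifts of 0.1 to 0.3 SD at baseline only, with r = 0.5, the bias is 0.10 to 0.30 SD for change and 0.05 to 0.15 SD for a baseline-adjusted contrast. With a persistent shift, the change bias vanishes. Expressing these as a share of the treatment effect would require an effect size that the plan does not give, so no such percentage is claimed.

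The differing descriptions of the population in sections {9} and {10} are a wording matter only. This is a change that should be made; it does not invalidate the trial.

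**What to change.** 1. Amend {6b} and {18a} so that all pre-operative questionnaires (KOQUSS-40, self-efficacy, physical activity) are completed on one common form in both arms before the allocation is generated or disclosed.
2. State that order in {16a} to {16c}, and check that Figures 1 and 3 agree. If the intended order is already baseline first, correcting the wording on the form is enough.
3. As a wording note, reconcile the population descriptions in {9} and {10}. Allocation need not be moved to after surgery.

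The cost is a minor reordering of steps at each site and a few sentences of protocol text; the sample size is unchanged. This cures the baseline only. The tablet and paper difference at the three later visits would remain and needs its own decision.
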